
## Remote monitoring, feedback, and dynamic prescription adjustment

3

Real-time data transmission: IoT devices will automatically transmit RMT data to the platform. Participants will log aerobic and resistance training completion via the application.Automated feedback and alert system: the application will deliver daily reminders, motivational messages, and visualized progress charts. Automated alerts will be generated and transmitted to the responsible therapist if a participant misses scheduled training sessions or if physiological parameters (e.g., SpO₂) fall below predefined thresholds.Clinician-led monitoring and dynamic adjustment: respiratory therapists will remotely review patient adherence and performance data on a weekly basis via the therapist dashboard. Feedback will be communicated through in-application messaging or telephone. In collaboration with supervising physicians, therapists will dynamically adjust PR prescriptions through the platform as clinically indicated (e.g., increasing RMT resistance, modifying aerobic targets), thereby establishing a continuous closed-loop management cycle.

### Outcome measures and assessment instruments

3.1

#### Primary outcome

3.1.1

##### The primary outcome is the 12-month rate of moderate-to-severe AECOPD

3.1.1.1

Defined as the number of moderate or severe acute exacerbation events occurring per patient during the 12-month follow-up period. AECOPD is defined as an acute deterioration of respiratory symptoms (dyspnea, cough, and/or sputum production) requiring treatment with systemic corticosteroids and/or antibiotics, or necessitating hospitalization (10). Exacerbation data will be ascertained through review of the hospital information system and confirmed via structured telephone follow-up.

#### Secondary outcomes

3.1.2

Exercise tolerance: assessed using the six-minute walk distance (6MWD), conducted in accordance with American Thoracic Society (ATS) guidelines along a 30-meter flat corridor. Measurements will be obtained at baseline and at 3, 6, and 12 months post-intervention.Dyspnea severity: evaluated using the modified British Medical Research Council (mMRC) dyspnea scale, a single-item, five-level ordinal scale (scored 0–4), with higher scores indicating greater dyspnea severity.Health-related quality of life: assessed jointly using the COPD Assessment Test (CAT) and the St. George’s Respiratory Questionnaire (SGRQ). The CAT comprises 8 items with a total score ranging from 0 to 40, where higher scores indicate worse HRQoL. The SGRQ comprises 50 items encompassing symptoms, activity limitation, and disease impact domains, with a total score ranging from 0 to 100, where higher scores indicate worse HRQoL.Pulmonary function: measured using a portable spirometer, capturing FEV₁ % predicted, FVC, and peak expiratory flow (PEF). All measurements will be performed by trained research nurses according to standardized operating procedures.Rehabilitation adherence: in the intervention group, adherence will be assessed using the following metrics: (i) *device utilization adherence rate*, defined as daily data upload completion rate ≥ 80%; (ii) *training completion rate*, calculated as the number of days on which prescribed rehabilitation was completed divided by the total prescribed training days, multiplied by 100%; and (iii) *follow-up completion rate*, defined as the proportion of participants completing assessments at each scheduled timepoint.Adverse events: all adverse events occurring during the study period will be systematically recorded, including but not limited to falls, fractures, or cardiovascular events associated with rehabilitation training; disease deterioration events; and unplanned healthcare utilization events.

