Internet of Things (IoT) technology, enabling real-time data exchange between patients and healthcare providers through interconnected devices and platforms, represents a significant advancement in contemporary healthcare delivery (16). Although IoT has been explored for continuous vital sign monitoring in COPD management (17–20), existing evidence for PR is limited, especially for patients with moderate-to-severe COPD and a history of exacerbations. Most studies are characterized by small sample sizes and short follow-up periods, precluding robust assessment of long-term clinical outcomes. Moreover, substantial heterogeneity in intervention design has hindered the development of a standardized IoT-based PR management model (21).

In response to these gaps, the present study aims to conduct a prospective cohort investigation to develop and evaluate an IoT-based PR management model and to assess its impact on clinical outcomes in patients with moderate-to-severe COPD. The specific objectives are as follows: (1) to compare the effect of an IoT-assisted PR management model versus conventional care on the rate of AECOPD-related readmissions within 12 months post-discharge; (2) to evaluate the model’s efficacy in improving exercise tolerance, dyspnea, HRQoL, pulmonary function, and rehabilitation adherence; and (3) to examine the safety and feasibility of IoT-assisted PR management, thereby providing evidence-based support for clinical practice.

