##### Follow-up assessments

2.5.1.3

Outpatient clinic visits will be scheduled at 1, 3, 6 and 12 months for clinical evaluation, spirometry, and questionnaire administration. No remote monitoring or proactive feedback regarding PR adherence will be provided during the follow-up period.

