#### IoT-enhanced pulmonary rehabilitation group (intervention group)

2.5.2

In addition to standard education and the initial PR prescription, participants in this group will receive a comprehensive IoT-based management model. The system architecture of IoT-based platform is illustrated in Figure 3.

IoT platform and devices: participants will be provided with an IoT-enabled threshold-load respiratory training device and a dedicated smartphone application (“Breathing Tribe,” patient-facing interface). A clinician portal and therapist application will facilitate remote management. A pulse oximeter will be provided to ensure exercise safety monitoring.Individualized prescription delivery via the platform: at discharge, clinicians will use the portal to generate personalized, dynamic PR prescriptions based on baseline assessment findings (e.g., 6MWT results, MIP), which will be electronically transmitted to the patient’s application. The prescription will encompass:

Respiratory muscle training (RMT): twice daily using the IoT device. Initial intensity will be set at 30% of MIP, with weekly increments of 5%, up to a maximum of 60% MIP. The device will automatically record training frequency, duration, and achieved inspiratory/expiratory pressures.Aerobic and resistance training: home-based walking prescribed at 50–60% of the average speed achieved during the 6MWT, combined with resistance band exercises (identical protocol to the control group). The application will provide instructional videos and a built-in timer.Medication and nutritional management: the application will incorporate medication reminders and deliver personalized dietary recommendations based on Nutritional Risk Screening 2002 (NRS2002) assessment results.

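### Group B is under much closer surveillance than Group A, and no common source is set for adverse events, so a between-group count of all recorded events risks detection bias

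*Protocol article*

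**What the plan says.** Section 3.1.2 lists adverse events among the secondary outcomes: "all adverse events occurring during the study period will be systematically recorded, including but not limited to falls, fractures, or cardiovascular events associated with rehabilitation". The same entry adds "disease deterioration events; and unplanned healthcare utilization events". Safety is part of the third objective in the Introduction: "to examine the safety and feasibility of IoT-assisted PR management".

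For Group A, section 2.5.1.3 states: "Outpatient clinic visits will be scheduled at 1, 3, 6 and 12 months for clinical evaluation, spirometry, and questionnaire administration". It continues: "No remote monitoring or proactive feedback regarding PR adherence will be provided during the follow-up period".

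For Group B, section 2.5.2 adds: "A pulse oximeter will be provided to ensure exercise safety monitoring". Section 3 adds "respiratory therapists will remotely review patient adherence and performance data on a weekly basis via the therapist dashboard", with feedback by message or telephone. It also says "Automated alerts will be generated and transmitted to the responsible therapist if a participant misses scheduled training sessions", and the same sentence extends the alerts to SpO2 below a threshold. The Discussion (section 4) describes daily data review and telephone follow-up by research nurses, and outreach when uploads stop for three days.

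Three other places bear on ascertainment. Section 3.1.1.1 finds exacerbations through hospital records and confirms them by structured telephone follow-up, without limiting this to one arm. Section 3.3 blinds outcome assessors as far as feasible. The limitations paragraph of the Discussion concedes possible detection bias, but attributes it to the lack of blinding.

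**The concern.** In a controlled study, listing adverse events as a secondary outcome invites a comparison of the arms. That comparison is fair only if an event has about the same chance of being recorded in either arm. Here the intervention is itself a surveillance system. A minor fall, a dizzy spell or a short desaturation at home has several routes to staff in Group B. In Group A it may surface only if the patient recalls it at a visit up to 26 weeks later.

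A higher count in Group B could then reflect closer observation rather than more harm, and a real reduction in events could be hidden. Covariate adjustment does not help, because it addresses differences between patients and not differences in capture. Blinding an assessor does not equalise which events reach that assessor.

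**Working it through.** The plan gives no adverse-event rate, power or capture probability, so there is no stated figure to reproduce. The check has two parts: the channels, which come from the document, and an illustration of size, which rests on assumptions.

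**1. Channels set side by side**

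- Both arms: follow-up at weeks 4, 12, 26 and 52 (Abstract). For exacerbations there is also hospital-record review and telephone confirmation (3.1.1.1).
- Group B only: oximeter (2.5.2); missed-session and SpO2 alerts, weekly therapist review, messages or calls (3); daily nurse data review and three-day outreach (4).
- Over 52 weeks this is 4 scheduled contacts in Group A, against the same 4 plus about 52 weekly reviews in Group B, before alerts, daily review and calls.
- Section 3.3 gives follow-up coordination and data entry to research nurses, and section 4 gives daily platform review to research nurses. The article does not say whether they are the same people, but nothing separates what the platform reveals from what is recorded.

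**2. Time from event to next scheduled visit, Group A**

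The gaps between visits are 4, 8, 14 and 26 weeks. The share of follow-up lying more than r weeks before the next visit is Σ max(0, gap − r)/52.

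- r = 4: (0 + 4 + 10 + 22)/52 = 36/52 = 69%.
- r = 13: (0 + 0 + 1 + 13)/52 = 14/52 = 27%.

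This counts scheduled visits only. The telephone follow-up for exacerbations is not included.

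**3. Relative capture (assumed recall model)**

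Assume that a non-hospital event is still reported with a probability that halves every h weeks. Then capture = Σ[(1 − e^(−λ·gap))/λ]/52 with λ = ln 2/h. For a weekly enquiry it is (1 − e^(−λ))/λ.

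- h = 13: Group A 0.655, weekly 0.974, ratio 0.67, apparent risk ratio 1.49.
- h = 26: 0.797, 0.987, ratio 0.81, apparent risk ratio 1.24.
- h = 52: 0.889, 0.993, ratio 0.895 (0.90 below), apparent risk ratio 1.12.

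The half-lives are assumptions. So is treating the weekly review as if it elicited events.

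**4. Probability that a two-sided 5% test rejects at equal true risk**

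Take n = 294 per group. The observed proportions are π in Group B and cπ in Group A, where π is the assumed true incidence and c the relative capture. Let d be their difference and p̄ their mean. Then SE0 = √[2p̄(1 − p̄)/n], SE1 = √[pA(1 − pA)/n + pB(1 − pB)/n], and P(reject) = Φ[(d − 1.96·SE0)/SE1] + Φ[(−d − 1.96·SE0)/SE1].

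Largest case, π = 0.30 and c = 0.67: 0.300 v 0.201, d = 0.099, SE0 = 0.0357, SE1 = 0.0355. (0.099 − 0.0700)/0.0355 = 0.82, so P = 79%.

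Smallest case, π = 0.05 and c = 0.90: 0.050 v 0.045, d = 0.005, both SEs 0.0175. P = 4.7% + 1.2% = 6%.

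| Assumed true incidence | c = 0.67 | c = 0.81 | c = 0.90 |
|---|---|---|---|
| 5% | 17% | 9% | 6% |
| 10% | 30% | 13% | 7% |
| 30% | 79% | 34% | 13% |

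With 267 per group, the number before the attrition allowance, the largest figure is 75% and the smallest is still 6%.

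**5. Cross-check with a different model**

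Take equal true event rates, assumed capture sA and sB, and a Wald test on the log rate ratio with variance 1/(nλ·sA) + 1/(nλ·sB), where λ is now the true event rate. Use n = 267 and 0.3 to 1.0 events per patient-year.

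- Capture 0.90/0.90: rate ratio 1.00, false-positive rate 5.0%.
- Capture 0.90/0.95: rate ratio 1.06, false-positive rate 6.2% to 9.2%.
- Capture 0.50/0.90: rate ratio 1.80, false-positive rate 85% to 100%.

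The direction is the same, the size depends wholly on the assumed capture, and the problem vanishes when capture is equal.

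**The case against.** The strongest reply is that the article promises systematic recording, and that the method of eliciting events belongs in the full protocol or case report form. The assessment schedule is in Supplementary Tables S1 and S2, which are not shown. Nothing says that Group A patients are not asked about adverse events. This stands as far as question wording, grading and coding go. It does not dispose of the point, because a visit schedule common to both arms would leave Group B's additional channels in place, and the outcome as worded takes in every event however it became known.

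A reader might infer more than the text supports:

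- That the comparison is biased. Only a risk of bias follows, because capture is unknown and may be nearly equal for hospital-recorded events.
- That adverse events are one undifferentiated outcome. The entry names three kinds.
- That Group A is seen only at four visits. Exacerbations are also sought by record review and telephone, and they overlap with deterioration and unplanned care.
- That a chi-square test of adverse events is planned. Section 3.4 is generic, and the safety objective is not worded as a comparison.
- That SpO2 alerts or therapist contacts are logged as events. No passage says so, although none excludes it.
- That only training-related falls count. That phrase describes examples and does not filter the set of all events.

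It is also fair to say that the weekly review concerns adherence and performance data, so near-complete Group B capture is unproven. And a bias that mostly overstates IoT harm is less dangerous than one that conceals it.

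**Conclusion.** The point holds as a risk of detection bias in any between-group comparison of non-serious or self-reported events, or of events known only through the platform. It rests on what the article itself fixes: unequal channels, an outcome that takes in all events, common ascertainment stated only for exacerbations, and a limitation that names blinding but not surveillance. The expected direction is mostly against IoT. Exacerbations and hospital-recorded events are less exposed.

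The size cannot be derived from the document. The range of 6% to 79% follows from assumed relative capture of 0.67 to 0.90, assumed incidence of 5% to 30%, full Group B capture and 294 per group. It shows that the effect could be negligible or large and is not an estimate. The point concerns a secondary outcome, and a purely descriptive safety report would soften it without removing it.

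**What to change.** Amend section 3.1.2 as follows.

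- Base the between-group adverse-event comparison only on sources common to both arms: the same structured questions at the existing week 4, 12, 26 and 52 contacts, plus hospital records.
- Record the source of each event in the EDC: scheduled contact, hospital record, platform alert or remote contact.
- Report events known only through the platform, the oximeter or an alert-triggered contact separately and descriptively for Group B. Do not count alert-triggered contacts as unplanned healthcare use in the comparison.
- Compare falls, fractures and cardiovascular events regardless of attribution to training, since session logs are described only for Group B.
- Add unequal surveillance to the limitations, beside the sentence on blinding.

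The cost is a wording change, one EDC field and one question set at contacts already scheduled, with no extra staff, visits or patients. Handling of events for patient care is unaffected. The downside is that some genuine mild Group B events leave the comparison, so the compared counts are smaller, although those events are still reported. The source of an event is hard to reconstruct later, so the field should exist before data collection.

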### Covariates

3.2

Baseline data will be systematically collected, encompassing: demographic characteristics (age, sex, educational attainment, living arrangements, and health insurance type); disease characteristics (COPD duration, GOLD grade, prior exacerbation history, and comorbidity burden quantified using the Charlson Comorbidity Index); smoking history; current pharmacological regimen; and baseline pulmonary function parameters. We acknowledge that allocation based on patient preference and technology readiness may introduce selection bias. Patients who are more comfortable with smartphones and IoT devices may also be younger, more educated, more motivated, more adherent, or have better social support. All of these factors could influence the outcomes. Therefore, the following additional variables will be collected to allow for statistical adjustment: digital literacy, baseline motivation, and socioeconomic status.

### Data collection and follow-up procedures

3.3

Dedicated research nurses will be appointed to oversee participant recruitment, baseline assessment, follow-up coordination, and data entry. Data will be collected and managed using the FREE Electronic Data Capture System (version 2.0; Beijing FreeClinical Medical Technology Co., Ltd., Beijing, China). All outcome assessors will be blinded to group allocation throughout the follow-up phase to the extent feasible. The schedule of assessments across follow-up timepoints is presented in Supplementary Tables S1, S2.

### Statistical analysis

3.4

Data will be analyzed using SPSS version 23.0 and R (version 4.2 or above). The following analytical approaches will be employed:

(1) Data description: continuous variables will be assessed for normality using appropriate statistical tests. Normally distributed data will be expressed as mean ± standard deviation (x̄ ± s); non-normally distributed data will be presented as median (interquartile range). Categorical variables will be summarized as frequencies (*n*) and proportions (%).(2) Between-group comparisons: categorical variables will be compared using the chi-square test or Fisher’s exact test, as appropriate. Normally distributed continuous variables will be analyzed using the independent samples t-test; within-group pre-post comparisons will employ the paired t-test. Non-normally distributed variables will be analyzed using non-parametric equivalents (Mann–Whitney U test or Wilcoxon signed-rank test). Multiple group comparisons will utilize one-way analysis of variance (ANOVA) with appropriate post-hoc correction (LSD or Bonferroni). Longitudinal data across repeated time points will be analyzed using repeated measures ANOVA or generalized estimating equations (GEE).(3) Multivariable analysis: to delineate the independent association between the IoT intervention and primary outcome measures (e.g., pulmonary function improvement, AECOPD frequency, readmission rate), multivariable logistic regression or Cox proportional hazards models will be employed, with adjustment for pre-specified potential confounders (including age, sex, comorbidities, and smoking history).(4) Missing data: missing data for key variables will be addressed using single and multiple imputation techniques to preserve sample integrity and maximize analytical efficiency.(5) Significance threshold: all statistical tests will be two-sided, with a significance level of *p* < 0.05. Where applicable, multiple testing corrections (e.g., Bonferroni correction) will be implemented to control the family-wise type I error rate.

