#### Inclusion criteria

2.2.1

Age between 40 and 75 years.A confirmed diagnosis of COPD according to GOLD criteria, defined as a post-bronchodilator FEV₁/FVC ratio < 0.70 and FEV₁ % predicted < 80% (GOLD grades 2–4) at enrollment.A history of at least two moderate acute exacerbations or one severe acute exacerbation requiring hospitalization within the preceding 12 months (Group E according to the GOLD guideline).Clinical stability for a minimum of four weeks prior to enrollment, defined as the absence of acute exacerbations or changes in pharmacological regimen.Capacity to provide written informed consent and willingness to comply with all study procedures, including utilization of IoT devices and the smartphone application.

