### Sample size calculation

2.3

The primary outcome measure is the 12-month rate of moderate-to-severe AECOPD. Based on prior literature, the annual exacerbation frequency in patients with moderate-to-severe COPD ranges from 0.5 to 3.0 events, of which approximately 60% are classified as moderate or severe. Assuming a two-sided significance level (*α*) of 0.05 and a statistical power (1 − *β*) of 0.80, and informed by preliminary data and published evidence suggesting that PR interventions reduce exacerbation frequency by approximately 20% (risk ratio [RR] = 0.80), sample size calculations performed using PASS 2023 software indicated a requirement of 267 participants per group. Accounting for an estimated attrition rate of 10%, which is considered feasible given the chronic disease management context in the Shijiazhuang region, a 10% inflation factor was applied, yielding a final required sample size of 294 participants per group and a total sample of 588 participants.

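### Section 3.4 names no rate-ratio model for the primary exacerbation count, and its normality rule would turn that count into a median and a rank test

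*Protocol article*

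**What the plan says.** Section 3.4, item (1), states that "continuous variables will be assessed for normality using appropriate statistical tests". If normality is rejected, "non-normally distributed data will be presented as median (interquartile range". Item (2) carries the same split into the tests: "Normally distributed continuous variables will be analyzed using the independent samples t-test", and "Non-normally distributed variables will be analyzed using non-parametric equivalents (Mann–Whitney U test or Wilcoxon signed-rank test". Item (2) also has a route for repeated measures that does not depend on normality: "Longitudinal data across repeated time points will be analyzed using repeated measures ANOVA or generalized estimating equations (GEE". Item (3) adds covariate-adjusted logistic or Cox models and lists exacerbation frequency, readmission and lung-function improvement among their targets.

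Section 3.1.1.1 fixes the primary outcome: "Defined as the number of moderate or severe acute exacerbation events occurring per patient during the 12-month follow-up period". Section 2.3 sizes the trial on a risk ratio of 0.80 for exacerbation frequency and gives the background rate: annual frequency "ranges from 0.5 to 3.0 events, of which approximately 60% are classified as moderate or severe".

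Two other places promise adjustment. Section 2.4 says baseline characteristics will be adjusted for in every later analysis. The Discussion says digital literacy and related factors will be adjusted for in the primary analyses.

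**The concern.** The plan lets a test on the trial's own data choose what is estimated. For the primary outcome, none of the routes listed in section 3.4 leads plainly to the quantity on which the trial is sized, a ratio of event rates.

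- Chi-square and Fisher tests are for categories.
- Repeated measures ANOVA and GEE are offered for data at repeated time points, whereas the primary outcome is one 12-month total per patient.
- In their usual form, logistic regression models whether any event occurred and Cox regression models time to the first. Neither gives a ratio of events per patient.
- That leaves the normality rule as the only unadjusted comparison of a numeric variable that fits.

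Under that rule a small count becomes a median with interquartile range and a Mann–Whitney p-value. At stake is whether the main result shows the effect at all, in units that match the design, and whether it can be adjusted in a study where patients' preference and technology readiness decide the group.

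**Working it through.** **Inputs.** From section 2.3: 0.5–3.0 exacerbations a year, about 60% of them moderate or severe, ratio 0.80, 267 per group before attrition. Control rate m = 0.5 × 0.60 to 3.0 × 0.60 = 0.3 to 1.8 per year; intervention rate 0.8m. The protocol gives no dispersion, so k = 0 (Poisson), 0.5 and 1.0 are assumed.

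**The plan's own figure.** 267 cannot be confirmed as a rate comparison, because no single control rate or dispersion is stated. With n = (1.96 + 0.84)² × (1/m + 1/(0.8m) + 2k) / (ln 0.8)², the Poisson requirement runs from 1,183 per group (m = 0.3) to 198 (m = 1.8), and 267 corresponds to m ≈ 1.33. It is used below only as the group size.

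**Step 1: population medians under a true ratio of 0.80.** The median passes from 0 to 1 where P(0 events) = 0.5. For Poisson this is m = ln 2 = 0.693; for the negative binomial it is m = (2^k − 1)/k. The intervention group reaches the same point when m is larger by a factor 1/0.8. The medians differ only between those two values. For Poisson they differ again above m = 1.678, where the control median becomes 2. The range is 1.8 − 0.3 = 1.5 wide.

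| Distribution | Control rates at which medians differ | Width | Share of range with equal medians |
|---|---|---|---|
| Poisson | 0.693–0.866 and 1.678–1.8 | 0.173 + 0.122 = 0.295 | 1 − 0.295/1.5 = 80.3% |
| k = 0.5 | 0.828–1.036 | 0.207 | 1 − 0.207/1.5 = 86.2% |
| k = 1.0 | 1.000–1.250 | 0.250 | 1 − 0.250/1.5 = 83.3% |

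Where they are equal, both medians are 0 or both are 1.

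**Step 2: does the count fail a normality test?** Simulation at 267 per group, with m = 0.3, 0.6, 0.9, 1.2, 1.5 and 1.8 crossed with the three dispersions (18 scenarios). Shapiro–Wilk, applied to the control group, rejected in every one of 200 simulated trials per scenario. The protocol does not name its test; Shapiro–Wilk is assumed.

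**Step 3: what the trial would print.** In 2,000 simulated trials per scenario, the two sample medians coincided in 12% to 100% of trials, and in more than 90% of trials in 13 of the 18 scenarios.

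**Step 4: what the rank test costs.** Power at a true ratio of 0.80, 267 per group:

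| Control rate | k | Mann–Whitney | Log rate ratio (Wald) |
|---|---|---|---|
| 0.3 | 0 | 0.23 | 0.24 |
| 0.9 | 0.5 | 0.44 | 0.51 |
| 1.2 | 0.5 | 0.52 | 0.59 |
| 1.8 | 0.5 | 0.59 | 0.68 |
| 1.8 | 1.0 | 0.42 | 0.53 |

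Over all 18 scenarios the loss is about 1 to 11 percentage points.

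**Step 5: adjustment.** A Mann–Whitney test has no place for covariates, and nor does the t-test on the other branch. Neither can deliver what section 2.4 and the Discussion promise.

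**The case against.** The strongest reply is that items (1) and (2) are the conventional descriptive, unadjusted layer. The rule is worded for continuous variables, and the text never sends the count through it. The adjusted analyses sit in item (3) and in the Discussion, which also mentions propensity scores and sensitivity analyses. Further detail may be in an analysis plan that is not shown.

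Part of this stands. Routing the count through the normality rule is an inference. But section 3.4 does not rank its routes, and where item (3) names exacerbation frequency it offers only logistic or Cox models. The point also rests on a rule the article states, not on detail it leaves out.

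A reader might infer more than the documents support:

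- **That FEV₁ fails normality by design because entry requires less than 80% predicted.** The limit applies only at entry ("GOLD grades 2–4) at enrollment"); follow-up values and changes are not cut. With assumed means of 45–60 and SDs of 12–18 at 267 per group, Shapiro–Wilk rejected for baseline FEV₁ in 7–100% of runs, for follow-up FEV₁ in 3–55%, and for change in about 5%, the nominal level. Mean and median at baseline differ by only 0.1–1.3 points.
- **That every outcome is affected.** Repeated outcomes such as FEV₁, six-minute walk distance, CAT and SGRQ have the GEE or ANOVA route, which does not depend on a normality result. GEE can give an adjusted mean difference.
- **That the mMRC scale goes through the rule.** Section 3.1.2 describes it as ordinal, and nothing assigns it there.
- **That the p-value hides the effect.** It does not: Mann–Whitney keeps most of the power. The median is what hides the effect.

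**Conclusion.** The point holds in a narrow form. A normality test on the trial data chooses both summary and test, and section 3.4 names no model that plainly estimates the rate ratio of 0.80 on which the trial is sized. If the primary count takes the one unadjusted numeric route that fits, it fails normality with near certainty and is reported as median and interquartile range. Those medians are identical in the population over 80–86% of the implied rates even when the intended 20% reduction is real. The loss is mainly one of estimation and adjustment: no rate ratio, no covariates, and about 1–11 points of power.

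This rests on the 0.3–1.8 range from section 2.3, on assumed dispersion of 0 to 1.0, on a test that behaves like Shapiro–Wilk, and on the inference about routing. For the continuous secondary outcomes the point is smaller: the plan already lists a suitable method in GEE but leaves the data-driven choice beside it. The change should be made.

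**What to change.** In section 3.4:

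1. Remove the normality test as a rule that decides summaries or tests.
2. Summarise exacerbations by group as events, patient-years and rate per patient-year with 95% CI. Estimate the effect as a covariate-adjusted rate ratio with 95% CI, from a negative binomial model or a Poisson model with robust standard errors, with log follow-up time as offset. The offset matters because 10% attrition is expected and section 2.2.3 withdraws patients during follow-up.
3. For the continuous secondary outcomes, state that the result is the mean difference with 95% CI from GEE or regression, adjusted for the collected covariates, whatever a normality test shows.
4. Keep medians and rank tests as descriptive or sensitivity output.

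The cost is analysis wording only; no new data or participants are needed. The downside is that skewed outcomes are reported as means, with the median available as a supplement.
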